## 5.5 General Concomitant Medication and Supportive Care Guidelines

In general, concomitant medications and therapies deemed necessary for the supportive care and safety of the subject are allowed, provided their use is documented in the subject records and on the appropriate case report form. If toxicity occurs, the appropriate treatment will be used to ameliorate signs and symptoms [including antiemetics for nausea and vomiting, anti-diarrheals for diarrhea and anti-pyretics (only if  $\geq 39^{\circ}\text{C}$  or lasting more

than 3 days) and anti-histamines for drug fever]. All supportive measures for optimal medical care will be given during the period of study.

There is a possible risk of anaphylaxis and Helixor® M should be administered in a setting where emergency treatment is available. Administration should be immediately discontinued and the appropriate therapy instituted if there is a serious allergic reaction. The patient must be observed in the clinic for at least 30 minutes after the lead in dose and for the first dose of the assigned dose level. Acute reactions (allergic or allergic-like reactions such as generalized itching, hives, rash, swelling of the face or throat, chills, difficulty breathing, shock or spasm of the airways) will be managed using standard therapy for acute drug reactions as per institutional standard of care and reported to the sponsor. If a grade 1 or 2 hypersensitivity reaction is suspected, this must be discussed with the IND sponsor and principal investigator before the patient is given another dose of Helixor® M. Patients developing grade 3 or 4 hypersensitivity will not receive another dose of Helixor® M.

#### Guidance on Infusion/Hypersensitivity Reactions:

Treatment recommendations are provided below and may be modified based on local treatment standards and guidelines as appropriate:

For grade 1 symptoms (mild reaction; infusion interruption not indicated; intervention not indicated):

Remain at bedside and monitor subject until recovery from symptoms. The following prophylactic premedications are recommended for future infusions: diphenhydramine 50 mg (or equivalent) at least 30 minutes before additional Helixor® M administrations.

For grade 2 symptoms (moderate reaction requires therapy or infusion interruption but responds promptly to symptomatic treatment [e.g., antihistamines, non-steroidal anti-inflammatory drugs, narcotics, corticosteroids, bronchodilators, IV fluids]; prophylactic medications indicated for  $\leq 24$  hours):

Stop the Helixor® M infusion, begin an IV infusion of normal saline, and treat the subject with diphenhydramine 50 mg IV (or equivalent) and/or acetaminophen 325 to 1000 mg; remain at bedside and monitor subject until resolution of symptoms. If the infusion is interrupted, restart the infusion at 50% of the original infusion rate when symptoms resolve; if no further complications ensue after 30 minutes, the rate may be increased to 100% of the original infusion rate. Monitor subject closely. If symptoms recur then no further Helixor® M will be administered at that visit. Administer diphenhydramine 50 mg IV, and remain at bedside and monitor the subject until resolution of symptoms. The amount of study drug infused must be recorded on the case report form (CRF). The following prophylactic premedications are recommended for future infusions: diphenhydramine 50 mg (or equivalent) and/or acetaminophen 325 to 1000 mg should be administered at least 30 minutes before additional Helixor® M administrations.

For grade 3 or grade 4 symptoms (severe reaction, grade 3: prolonged [i.e., not rapidly responsive to symptomatic medication and/or brief interruption of infusion]; recurrence of

symptoms following initial improvement; hospitalization indicated for other clinical sequelae [e.g., renal impairment, pulmonary infiltrates]; grade 4: (life threatening; pressor or ventilator support indicated):

Immediately discontinue infusion of Helixor® M. Begin an IV infusion of normal saline, and treat the subject as follows. Recommend bronchodilators, epinephrine 0.2 to 1 mg of a 1:1,000 solution for subcutaneous administration or 0.1 to 0.25 mg of a 1:10,000 solution injected slowly for IV administration, and/or diphenhydramine 50 mg IV with methylprednisolone 100 mg IV (or equivalent), as needed. Subject should be monitored until the investigator is comfortable that the symptoms will not recur. Helixor® M will be permanently discontinued. Investigators should follow their institutional guidelines for the treatment of anaphylaxis. Remain at bedside and monitor subject until recovery from symptoms. In the case of late-occurring hypersensitivity symptoms (e.g., appearance of a localized or generalized pruritis within 1 week after treatment), symptomatic treatment may be given (e.g., oral antihistamine, or corticosteroids).

Helixor® M induced fever should not be treated with antipyrexia agents including but not limited to (Acetaminophen or NSAIDs, etc) if less than 38.5°C. Prolonged fever beyond 3 days should be investigated for an alternative reason for fever.

Activation of pre-existing inflammatory irritation of superficial veins at the injection site may occur. In such cases, stop treatment temporarily until the inflammatory reaction has subsided.

The use of immunosuppressive systemic corticosteroids, immunosuppressive therapy, and growth factors including, but not limited to, granulocyte-colony stimulating factor (G-CSF), granulocyte macrophage-colony stimulating factor (GM-CSF), erythropoietin, etc. are prohibited while patients are on study. Patients are permitted to use topical, ocular, intra-articular, intranasal, and inhalational corticosteroids (with minimal systemic absorption). A brief course of corticosteroids for prophylaxis (e.g., contrast dye allergy) or for treatment of non-autoimmune conditions (e.g., delayed-type hypersensitivity reaction caused by contact allergen) is permitted. NSAIDs are to be avoided if possible. However, systemic steroid therapy is allowed for subjects on replacement therapy as long as prednisone  $\leq$  10 mg or its steroid equivalent.

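### Section 5.5 gives symptoms that recur after an infusion restart two different consequences: a stop for that visit only, or a permanent end to treatment

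*Protocol*

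**What the plan says.** The relevant text is in protocol section 5.5, under the guidance on infusion and hypersensitivity reactions.

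- **Grade 2 definition.** "moderate reaction requires therapy or infusion interruption but responds promptly to symptomatic treatment".
- **Grade 2 management.** The infusion is stopped and the patient treated. Then: "If the infusion is interrupted, restart the infusion at 50% of the original infusion rate when symptoms resolve". On recurrence: "If symptoms recur then no further Helixor® M will be administered at that visit". The branch ends by recommending, for future infusions, premedication that "should be administered at least 30 minutes before additional Helixor® M administrations".
- **Grade 3 definition, in the next paragraph.** The sentence is broken by a page boundary. Its first part describes a reaction that is "not rapidly responsive to symptomatic medication and/or brief interruption of infusion]; recurrence of", and it continues "symptoms following initial improvement; hospitalization indicated for other clinical sequelae".
- **Grade 3 or 4 management.** "Helixor® M will be permanently discontinued".

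Three other places state the consequence of a grade 3 or 4 hypersensitivity reaction. The opening text of section 5.5 and section 8.6 both say that such a patient gets no further dose. Section 5.6 lists the reaction among the events that end treatment. For a suspected grade 1 or 2 reaction, the opening text of section 5.5 leaves later dosing open, on condition that "this must be discussed with the IND sponsor and principal investigator before the patient is given another dose of Helixor® M".

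Section 5.4 makes a drug-related non-hematologic toxicity of grade 3 or higher a DLT, subject to listed exceptions, and a patient with a DLT stops study treatment.

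**The concern.** Take a patient whose reaction resolves, whose infusion is restarted as instructed, and whose symptoms then return. The grade 2 branch foresees exactly this sequence and ends dosing for the day. The grade 3 definition describes the same sequence and ends dosing for good. A reader at the bedside finds an instruction in the branch already being followed and has no prompt to look at the next paragraph.

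Two things are at stake. The first is safety: a patient whom the protocol excludes from further exposure could be given the drug again. Allergic and allergic-like reactions, including anaphylaxis, are named risks of the infusion (sections 5.5 and 7.6), so the situation is foreseeable. The second is the dose-finding result. Identifying the MTD is a primary objective, and grade 2 against grade 3 is the boundary of the DLT definition for non-hematologic toxicity. The trial is multi-center, so two sites could class the same event differently and both point to section 5.5.

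**Working it through.** There is no stated figure to reproduce. The check sets the passages side by side and then follows one event through the escalation table.

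**Step 1: does one event meet both descriptions?** The grade 2 branch permits a restart only when symptoms have resolved. Resolution is at least improvement. Any symptoms that return after the restart have therefore returned after an improvement, which is an item in the grade 3 list. The items in that list are separated by semicolons, and I read them as alternatives.

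**Step 2: compare the consequences.**

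| | Grade 2 branch | Grade 3 or 4 branch |
|---|---|---|
| Drug after recurrence | Stopped for that visit | Stopped permanently |
| Later infusions | Foreseen, with premedication; no exception for recurrence | None |
| General rule in 5.5 and 8.6 | Re-dosing possible after discussion | No further dose |
| Section 5.6 | Not in itself a reason to end treatment | Ends treatment |
| Section 5.4 | Not a DLT | DLT unless an exception applies |

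The two columns cannot both apply to the same patient.

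**Step 3: is the conflict confined to modifiable guidance?** The guidance opens by calling itself recommendations that sites may adapt to local standards. The bars on further dosing in the opening text of section 5.5, in section 5.6 and in section 8.6 carry no such qualification. Following the grade 2 text can therefore breach a rule that is not optional.

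**Step 4: effect on the 3+3 decision.** Let d be the number of patients with a DLT at a dose level. Regrading one patient's recurrence from grade 2 to grade 3 changes d to d + 1, provided that the event is drug-related, falls in the DLT period and is not covered by an exception. From the section 5.4 table:

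- 0 + 1 = 1 of 3: escalate becomes expand the level.
- 1 + 1 = 2 of 3: expand becomes stop escalation.
- 1 + 1 = 2 of 6: proceed becomes stop escalation, and section 13.1 then places the level above the MTD.

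**Step 5: limits on step 4.** Section 5.4 exempts hypoxia, syncope, high or low blood pressure, fever, chills and rigors when they settle within 24 hours of being treated. For those symptoms d does not change. It changes for symptoms outside the list, for example urticaria or bronchospasm, both of which section 7.6 names as reactions to the infusion. The move from single-patient cohorts to the 3+3 design is triggered by a drug-related toxicity of grade 2 or higher, so it occurs under either grading.

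**The case against.** The best defence is that the grade 2 text never assigns a grade to the recurrence. It gives the immediate bedside action. The premedication sentence closes the whole branch and serves mainly patients who had no recurrence. On this reading a recurrence moves the event to grade 3, the next paragraph takes over, and all that is missing is a cross-reference. In addition, the guidance is labelled as recommendations, and even a reaction left at grade 2 needs discussion with the sponsor and principal investigator before a later dose.

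Part of this stands. The silent-upgrade reading is possible, and the discussion requirement is a safeguard. But the text does not state the upgrade. It limits the stop to the visit and continues, in the same paragraph, to future infusions. The safeguard governs whether a grade 2 patient may be re-dosed; it does not settle whether the patient is grade 2. The recommendation label does not reach the bars elsewhere in sections 5.5, 5.6 and 8.6.

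It can also be said that grading follows CTCAE version 4.03 (section 7), and that section 5.4 does not refer to the management branches. That is true, and it means the DLT effect comes only through the grade. It does not remove the conflict in section 5.5: whichever grade is assigned, one of the two paragraphs there gives the wrong description or the wrong consequence for this event.

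A reader might go further and infer that restarting at the same visit breaches the requirement to discuss before another dose. The documents do not support that. An interrupted and restarted infusion reads naturally as the rest of the same dose: section 8.5 prepares one diluted solution per dose, and section 5.5 has the amount infused recorded. A general rule that a sub-branch does not repeat is not thereby contradicted.

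**Conclusion.** The concern holds as an internal contradiction about stopping treatment. For symptoms that return after a restart, section 5.5 supports both a stop for the visit and a permanent stop, and the permanent stop is backed by unqualified rules in sections 5.5, 5.6 and 8.6. It rests on two readings: that the items in the grade 3 definition are alternatives, and that resolution counts as initial improvement.

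The consequence for DLT counting is real but conditional. One regraded event moves 0/3 to 1/3, 1/3 to 2/3, or 1/6 to 2/6, and only for symptoms outside the section 5.4 exceptions. The documents give no rate of recurrence after restart, so an expected effect on the MTD cannot be calculated. It would go too far to say that section 5.4 contradicts itself, that every recurrence alters the DLT count, or that the accelerated phase is affected. None of these follows from the text.

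The point should be corrected because it bears on re-exposure of patients and on a primary objective, and because the repair is simple.

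**What to change.** Reconcile the grade 2 recurrence instruction in section 5.5 with the grade 3 definition and with the rules on further dosing in sections 5.5, 5.6 and 8.6. After the change, recurrence following a restart should have one grade, one treatment consequence and one DLT status. The premedication sentence should say whether it covers these patients, and the two branches should refer to each other. Which clinical rule applies is for the sponsor to decide.

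The cost is protocol amendment wording. Sample size, visits and data collection do not change. If patients have already been treated, any recurrence after restart should be checked against the agreed rule, so that DLT counts are consistent across sites.

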## **5.6 Duration of Therapy**

In the absence of treatment delays due to adverse event(s), treatment may continue until one of the following criteria applies:

- The patient or legal representative (such as a parent or legal guardian) withdraws consent for treatment
- Disease progression: Patients may be allowed to continue treatment if the Principal Investigator feels that the subject is receiving benefit based on the following criteria:
  - Investigator-assessed clinical benefit, and

- Subject is tolerating study drug.

The assessment of clinical benefit should take into account whether the subject is clinically deteriorating and unlikely to receive further benefit from continued treatment. The following criteria need to be taken into consideration:

- Absence of clinical symptoms and signs indicating disease progression.
- No decline in ECOG performance status.
- Absence of rapid progression of disease or of progressive tumor at critical anatomical sites requiring urgent alternative medical intervention.

All decisions to continue treatment beyond PD must be discussed with the Principal Investigator.

- Intercurrent illness that prevents further administration of treatment,
- DLT listed in **Section 5.4**,
- Grade 3 or 4 Helixor® M hypersensitivity reaction,
- Treatment delays lasting longer than 2 weeks due to a drug-related toxicity that does not resolve to a  $\geq$  grade 1 or baseline despite supportive treatment per standard clinical practice,
- If in the opinion of the Investigator, a change or temporal or permanent discontinuation of therapy would be in the best interest of the patient,
- Noncompliance with trial treatment or procedure requirements,
- Patient is lost to follow-up, or
- Patient becomes pregnant.

## **5.7 Duration of Follow Up**

Patients will be followed for 28 days after completion or removal from study or until death, whichever occurs first. Patients who are discontinued from the study treatment due to a drug-related AE will be monitored for safety until the resolution of the AE to  $\leq$  grade 1 or stabilization or until initiation of a new therapy for their cancer, whichever occurs first.

Patients who have completed or discontinued from treatment should be contacted every six months to monitor overall survival. Information of other cancer therapies after discontinuation from the study treatment will be collected.

## **5.8 Criteria for Removal from Study**

Patients will be removed from study when any of the criteria listed in **Section 5.6** applies. The reason for study removal and the date the patient was removed must be documented in the Case Report Form.

## **6. DOSING DELAYS AND SCHEDULING/DOSE MODIFICATIONS**

### **6.1 Dosing Delays and Scheduling/Missed Doses**

Helixor® M will be held for drug-related fever  $\geq 39^{\circ}\text{C}$ , chills, transient dizziness, or if the dosing criteria per **Section 5.2** are not met. If a delayed dose cannot be made up during the same week, it will be skipped. If toxicity does not resolve to  $\leq$  grade 1 or baseline within 2 weeks, trial treatment should be discontinued after consultation with the IND sponsor and principal investigator.

Patient-initiated, pre-planned missed doses (for example, due to vacation plans) are not permitted during the first 8 weeks of treatment. Missed doses due to clinic scheduling and holiday closures are permitted. Patients are allowed to move 1 treatment per week by 1 day (for example: MWF  $\rightarrow$  TWF). Helixor® M infusions may not be given less than 24 hours apart. In special cases, after a documented discussion with the PI, Helixor® M infusions may be given on three consecutive days (for example: MTW) as long as they are given at least 24 hours apart. Up to 3 missed doses of Helixor® M for every 12 doses will be permitted after week 8. Allowance of Helixor® M breaks of greater than 1 week will be decided on a case-by-case basis by the Principal Investigator.

### **6.2 Dose Modifications**

When the delay is due to drug-related toxicity, the patient may resume Helixor® M with a dose reduction to the next lower dose level. Only two dose reductions due to the same toxicity will be permitted. In the event of a third occurrence of the same toxicity which would require a dose interruption, study therapy will be discontinued permanently. No dose reductions are permitted for patients enrolled in Dose Level 1.

## **7. ADVERSE EVENTS: LIST AND REPORTING REQUIREMENTS**

This study will use the descriptions and grading scales found in the revised National Cancer Institute Common Terminology Criteria for Adverse Events (CTCAE) Version 4.03 for adverse event reporting that can be found at [http://ctep.cancer.gov/protocolDevelopment/electronic\\_applications/ctc.htm](http://ctep.cancer.gov/protocolDevelopment/electronic_applications/ctc.htm).

The Investigator or designee must completely and promptly record each adverse event using the CRF, regardless of relationship to study drug as determined by the Investigator. The Investigator should attempt, if possible, to establish a diagnosis based on the patient's signs and symptoms. When a diagnosis for the reported signs or symptoms is known, the Investigator should report the diagnosis, not the symptoms, as the adverse event.

Information about all adverse events, whether volunteered by the subject, discovered by investigator questioning, or detected through physical examination, laboratory test or other means, will be collected, recorded, and followed as appropriate.

All adverse events experienced by patients will be collected and reported from the first dose of the investigational agent, throughout the study, and will only be followed for 28 days after the maximal planned dose is administered unless there are ongoing problems thought to be related to the investigational agent.

Patients who have an ongoing adverse event related to the study procedures and/or medication(s) may continue to be periodically contacted by a member of the study staff until the event is resolved or determined to be irreversible by the investigator.

**Laboratory abnormalities:** Laboratory abnormalities present at the screening visit will be recorded as pre-treatment signs and symptoms. After study treatment administration, all grade 3 and 4 clinical laboratory results that represent an increase in severity from baseline will be reported as adverse events. A grade 1 or 2 clinical laboratory abnormality should be reported as an adverse event only if it is considered clinically significant by the investigator.

## 7.1 Definitions

### 7.1.1 Adverse Event (AE)

Adverse event is defined as any undesirable sign, symptom or medical condition occurring after starting the study drug (or therapy) even if the event is not considered to be related to the study. An undesirable medical condition can be symptoms (e.g., nausea, chest pain), signs (e.g., tachycardia, enlarged liver) or the abnormal results of an investigation (e.g., laboratory findings, electrocardiogram). Medical conditions/diseases present before starting the study treatment are only considered adverse events if they worsen after starting the study treatment (any procedures specified in the protocol). Adverse events occurring before starting the study treatment but after signing the informed consent form will not be recorded. Abnormal laboratory values or test results constitute adverse events only if they induce clinical signs or symptoms or require therapy.

### 7.1.2 Serious Adverse Event (SAE)

A serious adverse event is an undesirable sign, symptom or medical condition which:

- Results in death
- Is life threatening (defined as an event in which the subject was at risk of death at the time of the event; it does not refer to an event which hypothetically might have caused death if it were more severe)
- Requires inpatient hospitalization or causes prolongation of existing hospitalization (see note below for exceptions) for  $\geq 24$  hours
- Results in persistent or significant disability/incapacity
- Is a congenital anomaly/birth defect (note: reports of congenital anomalies/birth defects must also be reported on the Pregnancy Supplemental Form)
- Is an important medical event (defined as a medical event(s) that may not be immediately life-threatening or result in death or hospitalization but, based upon appropriate medical and scientific judgment, may jeopardize the subject or may require intervention [e.g., medical, surgical] to prevent one of the other serious

outcomes listed in the definition above.). Examples of such events include, but are not limited to, intensive treatment in an emergency room or at home for allergic bronchospasm; blood dyscrasias or convulsions that do not result in hospitalization.)

Events **not** considered to be serious adverse events are hospitalizations for the:

- Admissions as per protocol for a planned medical/surgical procedure or to facilitate a procedure
- Routine health assessment requiring admission for baseline/trending of health status (e.g., routine colonoscopy)
- Medical/surgical admission for purpose other than remedying ill health state and was planned prior to entry into the study. Appropriate documentation is required in these cases
- Admission encountered for another life circumstance that carries no bearing on health status and requires no medical/surgical intervention (e.g., lack of housing, economic inadequacy, care-giver respite, family circumstances, administrative).

